**Methods/designs:**

This study is designed as a multi-center, randomized controlled trial of patients aged 18–65 years who are scheduled to undergo surgical posterior fixation. Treatment by the conventional open approach or percutaneous minimally invasive approach will be randomly assigned. The primary outcome measure is postoperative pain, which will be measured using the visual analogue scale (VAS). The secondary outcome parameters are intraoperative bleeding, postoperative drainage, surgery time, length of hospital stay, SF-36, EQ-5D-5 l, HADS, pain medication, deambulation after surgery, intraoperative fluoroscopy time, vertebral segment kyphosis, fracture vertebral body height, compression of the vertebral canal, accuracy of the pedicle screws, and breakage or release of the implants. Patient will be followed up for 1, 2, 3, 6, 12 and 24 months postoperatively and evaluated according to the outcomes using clinical and radiological examinations, plain radiographs and computed tomografy (CT).

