### Primary outcome

In the analysis of the results regarding the outcomes, we will employ the relative risk (RR) and its 95% confidence interval (95% CI) and derived estimators, such as relative risk reduction (RRR), absolute risk reduction (ARR), risk difference (RD), number needed to treat (NNT), and number needed to damage (NND), emphasizing that in this clinical trial the intention-to-treat (ITT) principle will be used.. To verify the associations among the other variables, univariate analyses followed by multivariate analyses will be performed through logistic regression, also using RR and its 95% CI as association and magnitude estimators.

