### Secondary endpoints and safety profile

Considering the secondary outcomes (including minor and major adverse events [AE]), comparing the two groups (A versus B), and for comparing variables between groups A and B, when dealing with proportions, the chi-square test will be used, while for continuous variables the Student’s *t* test (if equal variances) will be used when dealing with averages or the Bonferroni e Benjamini-Hochberg test in the case of medians, in both cases, for independent samples. To minimize the interference of possible confounding variables (in both primary and secondary outcomes), all analyzes will be performed using necessary adjustments such as logistic regression, subgroup analyzes (age, sex, fracture type, duration of surgery, participant center, etc). A significance level of 5% shall be considered in all of the analyses described above.

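### Logistic regression is the only adjusted model the protocol names, and it does not suit the mostly continuous secondary outcomes

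*Protocol article*

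**What the plan says.** Three parts of the protocol article bear on the adjusted analysis.

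- **Secondary endpoints and safety profile.** The aim is stated as "To minimize the interference of possible confounding variables (in both primary and secondary outcomes"), and for that purpose "all analyzes will be performed using necessary adjustments such as logistic regression, subgroup analyzes", followed by a list of factors that ends in *etc*. The same paragraph compares continuous variables between groups with Student's *t* "test (if equal variances) will be used when dealing with averages", with a separate route for medians. The Statistical analysis section says much the same.
- **Primary outcome (statistical analysis).** For associations among the other variables, "univariate analyses followed by multivariate analyses will be performed through logistic regression, also using RR and its 95% CI". This sentence carries no *such as*.
- **Abstract, Methods/designs.** "The secondary outcome parameters are intraoperative bleeding, postoperative drainage, surgery time, length of hospital stay, SF-36" opens the list of secondary outcomes. Further on come "intraoperative fluoroscopy time, vertebral segment kyphosis, fracture vertebral body height, compression of the vertebral canal, accuracy of the pedicle screws".

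No linear regression, analysis of covariance, mixed model or quantile regression is named anywhere. The only cut-off on any outcome scale is the two-point VAS reduction under Sample size, which concerns the primary outcome.

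**The concern.** Binary logistic regression, and any relative risk, needs an event. Blood loss, length of stay, SF-36, HADS, kyphosis angle and vertebral height have no event until someone chooses a threshold, and the protocol gives none for them. So the one model it names for adjustment cannot be applied directly to most of the outcomes it is meant to adjust.

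Two things are at stake. If an analyst forced these outcomes into the named model, information would be lost and the adjusted result would be a ratio for exceeding a threshold, while the unadjusted result is a difference in means. The two could not be compared as adjusted and unadjusted estimates of one effect. If the analyst did not force them, the only specified between-group comparison is an unadjusted one. That leaves unused the precision available from pre-operative values the trial already collects.

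**Working it through.** **1. Type of outcome.** The abstract lists 15 secondary outcomes; the Secondary outcomes section adds the Roland Morris questionnaire and Dennis's work scale, making 17. Checked against Table 2 (pre-operative variables):

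| Group | Outcomes | Number |
|---|---|---|
| Continuous or score, pre-operative value in Table 2 | SF-36, EuroQol, HADS, segment kyphosis, vertebral body height, canal compression | 6 |
| Continuous, count or score, no pre-operative value in Table 2 | bleeding, drainage, surgery time, fluoroscopy time, hospital stay, Roland Morris | 6 |
| Categorical, or type not evident | pain medication, deambulation, screw accuracy, implant breakage or release, work scale | 5 |

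So 12 of 17 are not binary, and 6 of those 12 have a pre-operative value.

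**2. The plan's sample size.** The illustration uses 58 per arm. For 50% versus 25%, two-sided 5% and 80% power, the pooled two-proportion formula gives [1.96·√(2·0.375·0.625) + 0.84·√(0.25 + 0.1875)]² / 0.25² ≈ 57.6, so 58. The stated number is reproduced this way. The model-choice point does not depend on it.

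**3. What dichotomising would cost.** Assumptions, none from the protocol: normal outcome, true difference d = 0.5 SD, one baseline covariate correlated 0.5 with the outcome, two-sided 5%, n = 58 per arm.

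- *t test:* power ≈ Φ(d·√(n/2) − 1.96) = Φ(0.5·√29 − 1.96) = Φ(0.733) ≈ 0.77. Simulation gives 77–78%.
- *Analysis of covariance:* the residual SD shrinks by √(1 − 0.5²) = 0.866, so d becomes 0.577 and power ≈ Φ(0.577·√29 − 1.96) = Φ(1.15) ≈ 0.87. Simulation gives 87%.
- *Median split, no covariate:* the proportions above the cut are Φ(0.25) = 0.599 and 0.401, and a two-proportion test has power of about 57%.
- *Median split, logistic regression with the covariate:* simulation gives 64–66%. This is the fair comparator for an adjusted analysis.

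| Analysis, 58 per arm | Power |
|---|---|
| Adjusted logistic regression, median split | 64–66% |
| Unadjusted t test | 77–78% |
| Analysis of covariance | 87% |

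Allowing for the 28% drop-out stated under Sample size, 58 × 0.72 = 41.8, about 42 per arm. The same ordering holds: about 50–52%, 61–62% and 74%.

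**4. Dependence on the cut-off.** Without a covariate, at 58 per arm and d = 0.5, a cut 1 SD from the midpoint compares 22.7% with 10.6%, and power is 42%. A cut 1.5 SD away compares 10.6% with 4.0%, and power is 27%. The result would depend heavily on a threshold the protocol does not define.

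**The case against.** The strongest reply is that the text is open. *Such as* and *etc* make logistic regression an example, so linear regression is permitted. The firmer sentence in the Primary outcome section is limited to associations among the other variables and is not presented as the model comparing the arms on secondary outcomes. Model detail for secondary outcomes is often left to an analysis plan, which is not shown. The unadjusted comparisons are on the original scale and unaffected. All of this stands.

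A reader might therefore go too far in two ways. One is to infer that the adjusted comparison of continuous outcomes must be made on cut-offs or cannot be made at all. The documents do not support that: the list is illustrative, subgroup analysis is named beside it, and no sentence plans to dichotomise a secondary outcome. The other is to infer an inflated false-positive rate from picking the most favourable cut-off. Nothing in the protocol plans a search over cut-offs.

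Two parts of the reply do not carry. Subgroup analysis, as described under Complications, adverse events, and additional surgery, tests the association within separate subgroups, so it does not supply one adjusted overall comparison. And the point is not silence alone: the article does name a model, offers it for all analyses, and names one that does not fit most of them.

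The gain from adjustment is also uneven. The 87% assumes a useful baseline covariate. Half of the 12 outcomes have no pre-operative value, and for those the gain would rest on weaker predictors.

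**Conclusion.** The point holds as a mismatch between the named adjusted model and the outcomes. Logistic regression is the only regression model in the document, it is offered for all primary and secondary analyses, and it does not suit about 12 of 17 secondary outcomes. Their specified comparison on the original scale is unadjusted.

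Under the stated assumptions, moving from the t test to an adjusted logistic model at a median split would cost roughly 11 to 14 percentage points of power at 58 per arm. Moving to analysis of covariance would gain roughly 9 to 10. Both figures are illustrative: the loss occurs only if outcomes are dichotomised, and the gain depends on the assumed correlation of 0.5.

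Severity is low to moderate. The primary outcome is a separate matter, and the unadjusted secondary comparisons are unaffected. The change is still worth making, because it replaces an ill-suited model and an unadjusted test with a more precise analysis at almost no cost.

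**What to change.** State in the analysis section that adjusted comparisons of continuous secondary outcomes use linear regression:

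- **Where a pre-operative value is collected** (SF-36, EuroQol, HADS, kyphosis, vertebral height, canal compression): analysis of covariance on that value, or a mixed model where the outcome is measured at several visits. Canal compression is read on CT, which is not repeated at the follow-up visits, so analysis of covariance suffices there.
- **Where none exists** (bleeding, drainage, surgery time, fluoroscopy time, stay, and Roland Morris, which Table 2 does not list): linear regression on pre-randomisation covariates only, on the log scale if skewed. Fracture type, centre, age and sex qualify. Duration of surgery, which the protocol lists among its factors, does not.

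Report adjusted mean differences with 95% confidence intervals (ratios of geometric means where logs are used). Keep logistic or log-binomial regression for truly binary outcomes such as implant breakage, loosening and adverse events.

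One detail to settle at the same time: the Outcome measurements section has the Table 2 variables acquired after allocation, while Patient selection places baseline outcome scores around consent. Patient-reported baselines used as covariates are best obtained before the allocation is known.

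The cost is one or two sentences and no new data. The only change in reporting is that continuous outcomes appear as adjusted mean differences and not as relative risks.

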### Ethical considerations

The study was approved by the Institutional Review Committees (IRCs) of all participating centers that agreed with the proposed study protocol (Trial registration: NCT03316703). Informed consent will be obtained before randomization, and the patients are free to refuse participation. The patients will not receive financial rewards for taking part in the study, and they are free to withdraw from the study at any time without interruption of their treatment and medical care.

## Discussion

Surgical treatment of thoracolumbar fractures traditionally has been performed mainly using an open midline approach involving fixation of the fracture with a pedicle screw-rod system associated with posterolateral bony fusion [4, 5].

Percutaneous pedicle screw fixation (PPSF), which initially was used for the treatment of degenerative spinal diseases, was introduced as an alternative for the treatment of thoracolumbar fractures [6]. PPSF is associated with less intraoperative blood loss, postoperative pain and paravertebral muscles damage [12–15]. However, the radiation exposure and surgery costs are higher [7, 13].

The difference between traditional open and percutaneous minimally invasive surgery for the treatment of thoracolumbar fractures remains controversial, and few randomized trials have been reported in meta-analyses and systematic reviews. Only four randomized studies were reported in the meta-analysis that reported better functional and radiological outcomes of the percutaneous approach than the long-term open approach [9]. Posterolateral bony fusion cannot be performed in PPSF; however, similar clinical and radiological results have been reported between fusion and non-fusion approaches for the posterior fixation of thoracolumbar fractures [16, 17]. The non-fusion concept has been extended to type B1 fractures with good results [13, 18].

The effect of minimally invasive percutaneous pedicle screws is similar to that of traditional open surgery. However, reduced trauma, less bleeding, a shorter operation duration, rapid post-operative recovery, less pain and reduced costs have been reported for PPSF [8, 19]. However, reports concerning the economic costs of minimally invasive surgery for thoracolumbar fractures are controversial because both lower [8] and higher economic costs [7] have been reported for PPSF.

Recently, percutaneous posterior fixation of thoracolumbar fractures has been introduced as an alternative to traditional open posterior fixation. The percutaneous approach presented better results for some clinical and radiological outcomes than the open approach and even reduced the complication rate [20]. However, more high-quality, randomized trials are required to confirm the best option for surgical treatment of thoracolumbar fractures.

## Data Availability

Not applicable in the section.
